## Abstract

Mobile health platforms have shown promise in the management of various mental health conditions (including stress, anxiety, and depression) and cognitive behavioral strategies emerged as a popular and effective option offered by the platforms. This paper presents the protocol of a study aimed to test the effectiveness of a mobile platform that uses cognitive-behavioral strategies for stress self-management in the Tuscany region (Italy). The mobile app is adapted to the specific needs of each vulnerable population for which it is designed: young and older people, healthcare professionals, entrepreneurs. The app will be evaluated on the following outcomes: (i) perceived susceptibility and severity of the pandemic situation, perceived benefits, and costs of preventive health behaviors, (ii) knowledge about Covid-19 preventive behaviors and negative consequences of social distancing, (iii) stress and psychopathological symptoms (i.e., anxiety, depression, and post-traumatic stress symptoms) and cognitive distortions. If successful, we expect that the platform could give various groups clinical benefits by providing symptom self-monitoring and early intervention, consolidating the number of mental health programs available, and decreasing barriers to treatment-seeking. This population-level approach has the potential to improve mental health outcomes in pandemic periods for many people.

## Introduction

### Background

The Covid-19 pandemic has caused a worldwide health crisis. Italy was the first western country to be affected by Covid-19 and, since the first confirmed case on February 20, 2020, this disease dramatically impacted the Italian society. Indeed, in March 2020, the Italian government established extraordinary preventive measures such as quarantine, lockdown, and physical distancing (Italian Ministry of Health, 2020). Gradually, thanks to the vaccination campaign, pandemic-induced stress regarding risk of infection, inadequate access to protective devices, and prolonged social isolation mitigated and the spread of the infection decreased (Davico et al., 2021; Prati and Mancini, 2021; Medda et al., 2022). The Covid-19 pandemic has had a significant impact on people’s everyday life and negative implications for mental health in the general population. In particular, low mood, irritability, anger, insomnia, emotional exhaustion, depression, anxiety, and stress have been variably but largely reported during the outbreak of Covid-19 all over the world (i.e., Brooks et al., 2020; Mazza et al., 2020; Odriozola-González et al., 2020; Salari et al., 2020; Pan et al., 2021; Wang et al., 2021; Medda et al., 2022). Locations hit hardest by the pandemic in 2020 had the greatest increases in prevalence of depressive and anxiety disorders (COVID-19 Mental Disorders Collaborators, 2021). Despite a wide and varying prevalence of mental health problems and psychosocial consequences across countries and regions, as Nochaiwong et al. (2021) highlighted, the global prevalence of depression was 28.0%, anxiety was 26.9%, and the rate of stress was 36.5%. The pandemic accounted for a global increase of 27.6 and 25.6% of cases of major depressive disorder and anxiety disorders, respectively. Daily Covid-19 infection rates and reductions in human mobility were associated with increased prevalence of major depressive disorder and anxiety disorders (COVID-19 Mental Disorders Collaborators, 2021). Levels of anxious-depressive symptoms were lowest when covid-19-related restrictions were lifted and highest when restrictions were in place (Moulin et al., 2023). Consequently, implementing empirically supported strategies to assist in managing stress and minimizing concomitant mental health problems has become a priority.

## Vulnerable/at risk populations for COVID-19 related psychological distress

Certain risk factors for the development of Covid-19-related psychological distress and other psychological symptoms have been found (for a review see Brooks et al., 2020). It has been shown that economic (i.e., unemployment, loss of job) and social (i.e., social distance, mandatory use of the masks, online learning) factors are strongly associated with Covid-19-related distress among young people, despite their relatively low risk of virus-related health complications (Jung et al., 2020; McGinty et al., 2020; Pierce et al., 2020; Roma et al., 2020; Shanahan et al., 2020; Rossell et al., 2021; Varma et al., 2021). Evidence also suggests that older adults – particularly those with previous comorbid health conditions or cognitive impairment – might be at risk of psychological symptoms due to prolonged isolation and anxiety about infection risk (Chong et al., 2020; Forlenza and Stella, 2020; Girdhar et al., 2020; Peyman and Olyani, 2020; Roma et al., 2020). Moreover, they are expected to adhere to preventive measures and restrictions for extended periods, to reduce the risk of contracting the infection. Healthcare workers also deserve special attention as a potential vulnerable population (Naushad et al., 2019; Brooks et al., 2020; Mahmud et al., 2021) as during the Covid-19 pandemic they have had to cope with an increasing workload, fear of infection, contagion and transmission to their families, frustration, highly challenging decisions, guilt and bereavement, intrusive thoughts, nightmares, physical exhaustion, and inadequate personal equipment (Elbay et al., 2020; Holmes et al., 2020; Krystal, 2020; Lasalvia et al., 2021). These experiences have impacted their mental health leading to symptoms of depression, anxiety, and distress (Kisely et al., 2020; Pappa et al., 2020; De Kock et al., 2021; Mahmud et al., 2021). In fact, when assessed with psychiatric diagnostic interviews during the pandemic, health care workers reported a prevalence of 14.3% for Generalized Anxiety Disorder, 13.7% for Depression, and 7.9% for Post-Traumatic Stress Disorder (PTSD). These prevalence estimates were lower when compared to screening instruments (Scott et al., 2023). Although the occurrence of mental health symptoms remained equally high between the first (March until June 2020) and the second surge (October 2020 to June 2021), Intensive Care Unit (ICU) nurses were more likely to experience work-related fatigue (Heesakkers et al., 2023).

Finally, the economic impact has been likewise devastating, forcing entire professional sectors (such as tourism, hotels, sports, entertainment, restaurant) to stop working. In this regard, entrepreneurs might represent another underestimated vulnerable population (Patel and Rietveld, 2020; Weems et al., 2020; Grandi et al., 2022). Therefore, the emotional responses triggered by the pandemic and their management appear substantial among vulnerable groups, such as young adults, older people, frontline and non-frontline healthcare workers, and entrepreneurs (Ho et al., 2020; Qiu et al., 2020; Trumello et al., 2020; Lasalvia et al., 2021; Wang et al., 2021).

## Theory-driven/evidence-based interventions for reducing psychological distress during COVID-19 pandemic

During the Covid-19 pandemic, the Health Beliefs Model (HBM; Becker and Maiman, 1975) has been found to be effective in promoting preventive health behaviors (Chen et al., 2019; Mukhtar, 2020; Tong et al., 2020; Carico Jr. et al., 2021; Jose et al., 2021; Wong et al., 2021) including hand washing, face mask wearing, maintaining social distance (Li et al., 2021), and receiving vaccination (Hossain et al., 2021). The HBM consists of six main aspects: (i) perceived susceptibility, (ii) perceived severity of getting an infection and perceived likelihood of disease transmission, (iii) perceived benefits of taking action to reduce the risk or seriousness of impacts, (iv) perceived barriers to taking action such as tangible and psychological costs of the advised action, (v) cues to actions or strategies to enhance one’s responsiveness, and (vi) individual, demographic, and psychosocial characteristics, which can affect perceptions of health-related behaviors (Janz and Becker, 1984; Kim et al., 2012; Chen et al., 2019; Jose et al., 2021). Overall, HMB-based interventions mitigate behaviors influenced by perceived health threats which provoke anxiety and fear, reinforcing individuals’ perceived benefits and self-efficacy (Janz and Becker, 1984; Kim et al., 2012).

Among the evidence-based strategies, Cognitive Behavioral Therapy (CBT) techniques for reducing Covid-19 related psychological distress have shown promising results (Aminoff et al., 2021; Sharrock et al., 2021; Song et al., 2021). Within the CBT framework, unhelpful ways of thinking and cognitive distortions are both risk and maintaining factors for psychological and psychiatric symptoms (Beck, 1963, 1979; Taylor, 2019). More specifically, people normally experience events according to their personal core beliefs which in turn lead to automatic thoughts, and typical emotional and behavioral responses. In case of negative core beliefs and subsequent negative automatic thoughts, any sort of event might result in negative emotions and maladaptive behaviors, maintaining poor mental states (Burns, 1980; Mathews et al., 1997; Rnic et al., 2016). Common cognitive distortions include *catastrophizing, overgeneralization*, and *minimizing the positive* (Burns, 1980).

## Use of mobile technology for health interventions

Mobile technology represents an available and attractive channel for health interventions (Donker et al., 2013; Beiwinkel et al., 2017). Digital health technologies have been utilized to manage numerous psychological symptoms such as depression, anxiety, and stress, major mood disorders, substance use, eating disorders, self-harm, and suicidal ideation (Witt et al., 2017; Hwang and Jo, 2019; Storm et al., 2021; Torous et al., 2021; Amanvermez et al., 2022); nonetheless, therapist supported/guided or blended interventions appeared more effective than unguided approaches (Harrer et al., 2018; Linardon et al., 2019; Taylor et al., 2021).

In addition, COVID-19 pandemic has transformed the context for e-health technologies (Torous et al., 2021). During the Covid-19 outbreak, several countries employed various digital health strategies to control the pandemic course. These digital health strategies, especially mobile health technology, significantly support health care systems by promoting self-surveillance, self-monitoring, self-efficacy, and high quality freely available resources (Fagherazzi et al., 2020; Inkster et al., 2020; Kalhori et al., 2021). Finally, resorting to mobile health technology might constitute a wide dissemination tool of treatment information and mental health preventive strategies (Green et al., 2021; Figure 1).

**Figure 1 fig1:**
[figure not shown]
MOST platform.

## Rationale

When lockdowns began in early 2020, few of us imagined the long road ahead. The Covid-19 pandemic shed light on our vulnerabilities. In fact, we believe that the post-pandemic period is a fruitful moment to analyze and increase awareness regarding emotions, thoughts, and behaviors emerged during the pandemic (Maggi et al., 2022). Pitel and Ballová Mikušková (2021) highlighted the need to explore the development of cognitive distortions and their stability during prolonged health threatening situations (i.e., Covid-19 pandemic), in which negative and unwarranted beliefs predict maladaptive behaviors and psychological symptoms (Čavojová et al., 2020; Somma et al., 2020; Aureus et al., 2021; Pavela Banai et al., 2021; Teovanović et al., 2021).

With this in mind, we decided to adopt CBT techniques to help individuals transform maladaptive strategies into functional coping mechanisms to manage the post-pandemic “normality” and prevent the worsening of potential long-term Covid-19-induced psychological difficulties. Keeping in mind the potential benefits offered by e-health technologies, we adhere to the available literature and the WHO recommendations. In fact, mobile self-monitoring and self-management strategies could stimulate learning about personal mental health, empower individuals to assume a more active role in their health care, and promote the development of functional mental health strategies (Kenny et al., 2016; Beiwinkel et al., 2017; Inkster et al., 2020; Green et al., 2021). In fact, the use of mobile technologies in mental health has been encouraged by the World Health Organization (2021) to promote psychological treatment and self-monitoring of mental health, providing tailored feedback to support a positive change. In addition, self-management seems to help people to identify the need for clinical approaches, providing potentially preventive interventions (Karasouli and Adams, 2014; Taylor et al., 2020).

### Objectives

The direct and indirect psychological and social effects of the Covid-19 pandemic are pervasive, affecting individuals’ mental health now and in the future (Holmes et al., 2020; Mahmud et al., 2021). Therefore, the successful use of quarantines and other preventive measures on behalf of public health requires reducing, as far as possible, the negative effects associated with it, including psychological distress (Brooks et al., 2020). Furthermore, the presence of Covid-19-related cognitive distortions shows the need for early intervention, which is a primary concern in health care (Aureus et al., 2021).

The present paper describes the protocol of the Mobile Opportunity against Stress (MOST) study, which will aim to test the effectiveness, in the post-pandemic era, of a mobile platform for stress self-management adapted to the needs of specific vulnerable populations: young adults, older individuals, frontline and non-frontline healthcare professionals, and entrepreneurs. These groups were selected as representatives of populations characterized by a different level of contagion risk and, therefore, exposed to a different level of stress. The potential differences in the mobile app usage and effectiveness between the specific vulnerable populations recruited will also be explored. The mobile app will help at monitoring personal Covid-19-related negative emotions and distress, raising awareness and knowledge about the pandemic course and the health-promoting behavior’s, and enhancing functional coping strategies and self-efficacy beliefs to reduce Covid-19 related stress and psychological difficulties.

### Trial design

The effectiveness of the smartphone app will be investigated through a single-group longitudinal research design. No control group will be included due to the open trial design of the study.

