### Outcomes

The effectiveness of the mobile app will be evaluated on the following outcomes: (i) perceived susceptibility and severity of the pandemic situation, perceived benefits, and costs of preventive health behavior’s (such as using a mask), (ii) knowledge about Covid-19 preventive behavior’s and negative consequences of social distancing, (iii) stress and psychopathological symptoms (i.e., anxiety, depression, and post-traumatic stress symptoms) and cognitive distortions.

These variables will be measured at a baseline assessment (i.e., each participant will complete the questionnaires within 2 weeks before using the app), at an intermediate evaluation (i.e., 2 months after the baseline evaluation), at a post-test evaluation (i.e., 4 months after the baseline evaluation), and at a follow-up evaluation conducted 6 months after the baseline assessment. The endpoint consists of the variation in depressive, anxious and stress states, cognitive distortions, and coping strategies, from the baseline to the intermediate, post-test and follow-up evaluations. The scores in all questionnaires that measure the endpoints will be aggregated in the form of mean scores with relative standard deviations at every evaluation. No harm derived by the use of the self-help application is expected.

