#### Recruitment

Participants’ enrolment will last for 2 months. During participants’ recruitment, a series of meetings will be organized, respectively in the healthcare services, universities, tourism and fitness industry associations, older people’s associations, to disseminate the study’s aims, and encourage participation. A website will be created to disseminate the study’s aims and online brochures about the study will be sent to the email addresses of Department directors of healthcare services, representatives of university students, representatives of industry associations and representatives of elderly associations, respectively. Eligible participants will be emailed the link through which they can download the smartphone application.

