Our study samples will be large and heterogenous and will include subjects with different ages: from young adults over 18 years to elderly individuals. So, the mobile platform for stress-self management will not be restricted for use and application with the target vulnerable populations, but it can also be transferred to other populations and contexts. If successful, we anticipate the platform could have clinical benefits to various groups by providing symptom monitoring and early intervention and decreasing barriers to treatment-seeking. In fact, the population-level approach has the potential to improve mental health outcomes in pandemic periods for many people. If this protocol is proven effective, it can be expanded to any population at risk of experiencing mental distress during a continuous public health emergency such as the Covid-19 pandemic.

Moreover, if effective, this application could also be implemented in other similar contexts in which stress management could be particularly helpful like in the business and school sectors. Non-healthcare workers, high school students, and teachers present similar characteristics to those of our population and could benefit from an app targeting.

Although the current protocol is addressed solely to Italian-speaking individuals, a future potential expansion could involve the integration of facilitators to reach underserved people from other ethnic groups.

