### Trial status

The current protocol is version 1 of 04-11-2022. It is estimated that patient recruitment will begin in February 2023 and will be completed around September 2023. Currently, we are approaching the pilot phase of the study that will begin in December 2022.

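### With no unexposed comparator, the single-group design cannot attribute change to the app, so the effectiveness aim and the talk of proof should be restated as change during app access

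*Protocol article*

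**What the plan says.** The Objectives section describes a study "which will aim to test the effectiveness, in the post-pandemic era, of a mobile platform for stress self-management". Trial design adds: "The effectiveness of the smartphone app will be investigated through a single-group longitudinal research design", and then: "No control group will be included due to the open trial design of the study".

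Under Outcomes, measurements are taken at baseline and at 2, 4 and 6 months, and "The endpoint consists of the variation in depressive, anxious and stress states, cognitive distortions, and coping strategies, from the baseline" to those later visits.

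Under Statistical methods for primary and secondary outcomes, the model is a repeated measures ANCOVA. Baseline scores are covariates, target group is the factor, and the timepoint scores are the dependent variables. The section on adherence strategies adds app use (weekly accesses and their mean duration) as a covariate.

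Anticipated results says: "If this protocol is proven effective, it can be expanded to any population at risk of experiencing mental distress" in a continuing public health emergency.

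The Background says of these same symptoms: "Levels of anxious-depressive symptoms were lowest when covid-19-related restrictions were lifted and highest when restrictions were in place".

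On timing, Recruitment says that "enrolment will last for 2 months", while Trial status says that "patient recruitment will begin in February 2023 and will be completed around September 2023".

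**The concern.** Testing effectiveness means attributing a change to the app. That needs some estimate of what would have happened without it, and the article plans no source for one. The reason given for having no control does not supply one either: open conduct does not rule out a concurrent or waiting-list comparison.

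The article itself names a rival explanation, since it reports that anxious and depressive symptoms move with pandemic restrictions. Some additional endpoints are perceptions of Covid-19 risk, which can also move with the epidemic whether or not anyone opens the app. Filling in the same self-report scales up to four times is a second rival explanation. Self-selection of people who feel unusually distressed at entry is a third, weaker one.

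At stake is what the trial may conclude. A significant time effect would show that scores changed. It would not show that the app changed them, and it would not support extending the app to other populations on the ground that it works.

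**Working it through.** **1. Does any planned contrast contain unexposed people?**

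- Time (Outcomes; Statistical methods): the same people before and after access. Baseline is unexposed but always earlier, so exposure and elapsed time coincide.
- Target group (Statistical methods): compares groups that all receive the app.
- App use (adherence strategies): use is at the participant's discretion and is observed after baseline. It separates heavier from lighter users, not users from non-users.

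None is an unexposed comparator. The article does not state this as a limit on its conclusion.

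**2. The plan's own figure.** Sample size gives at least 1,800 for a medium effect, 95% power and a level of 0.05. With eta-squared 0.06, f = sqrt(0.06/0.94) = 0.253. A noncentral-F search over 4 or 5 groups, 3 or 4 timepoints and several model variants gave 23 to 425. The largest, inflated for 48% dropout, is 425/0.52, about 818. So 1,800 is not reproduced from what is stated. That is a separate matter; here 1,800 serves only as the planned N.

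**3. How small a shared drift would look like an effect?** This is an illustration with a simple paired test, not the planned ANCOVA.

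- N = 1,800 (Sample size). The article cites dropout of up to 48% for apps aimed at depressive symptoms, so completers = 1,800 × 0.52 = 936. The planned carrying forward of last observations would keep dropouts in the analysis, so 936 is a completers-only case.
- Correlation rho between baseline and later score: not given; assumed 0.5, with 0.7 as a variant.
- SD of change = SD × sqrt(2(1 − rho)), which is 1.00 SD at rho 0.5 and 0.775 SD at rho 0.7.
- Smallest significant mean change = 1.96 × SD of change / sqrt(N).

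| | rho 0.5 | rho 0.7 |
|---|---|---|
| N = 1,800 | 1.96/42.43 = 0.046 SD | 0.036 SD |
| N = 936 | 1.96/30.59 = 0.064 SD | 0.050 SD |

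With a true app effect of zero, an assumed drift of 0.10 SD is significant with probability 0.99 to 1.00 at N = 1,800 and 0.86 to 0.98 at 936 (rho 0.5 to 0.7). For a drift of 0.05 SD the probabilities are 0.56 to 0.78 and 0.33 to 0.51.

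**4. Self-selection.** If volunteers started an assumed 0.2 SD above their usual level, the expected spurious fall would be 0.2 × (1 − rho), that is 0.10 SD at rho 0.5 and 0.06 SD at rho 0.7.

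**5. Could calendar time be separated from time on the app?**

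- Two-month window: the last baselines fall at month 2 and the first 4-month visits at month 4. There is no overlap.
- February to about September 2023: the first 4-month visits fall in June, so baselines from about June to September overlap them.
- Two months of enrolment plus six months of follow-up is eight months. From the start of February that ends at about the end of September, so Trial status may mean study completion. Its wording, however, is about recruitment.

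In the planned ANCOVA all dependent variables are post-baseline scores. A calendar-month term there would be fitted only to people who already have the app, and later entrants' baselines would contribute nothing as an unexposed trend.

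**The case against.** - **The design is declared openly.** A single-group study is a legitimate way to look at change under a new app, and Anticipated results also speaks of using pilot data to improve the next version. This stands: the choice of one group is not itself the error. The error is the claim attached to it.
- **The sentence on proof is conditional.** It stands under Anticipated results and is not a decision rule; no success rule is stated. A reader might infer that the plan commits to a roll-out after a significant result. The article does not say that. But the aim in Objectives and Trial design is not conditional, and it asks for the same attribution.
- **A fall without the app is not established.** A reader might infer from the Background that symptoms were bound to fall in 2023. They were reported lowest once restrictions were lifted, and the study is placed after the pandemic, so a further fall need not follow. Study setting mentions slow economic recovery, and the Rationale worries about worsening. Drift could imitate a benefit or hide one.
- **The drift figures are not from the planned test.** They use a paired test and an assumed correlation. A reader might add that such drifts lie far below the plan's own small effect. That depends on the conversion. Eta-squared 0.01 gives f = sqrt(0.01/0.99), about 0.10. Read as a two-group difference this is about 0.20 SD; read as a partial value for a paired contrast it is about 0.10 SD of change. The drift detected 95% of the time at rho 0.5 is 3.605/sqrt(N), or 0.085 SD at N = 1,800 and 0.118 SD at 936: close to the second reading, or above it. The comparison is not relied on.
- **Regression to the mean is weak here.** Eligibility sets no minimum symptom score and excludes acute episodes, so it could arise only through who volunteers.
- **Calendar adjustment is analysis-plan detail.** True, and its absence is not the finding. The finding rests on the aim, design and conclusion that the article does fix.

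**Conclusion.** The point holds as a mismatch between claim and design. The article sets out to test effectiveness and contemplates the app being proven effective and expanded, while no planned contrast can separate an app effect from calendar trend, retesting or, less strongly, self-selection. This conclusion needs no assumption about drift.

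The illustration shows only that samples of this size are sensitive to small shared changes: about 0.046 SD (N = 1,800) or 0.064 SD (936 completers) would be significant with no app effect, given an assumed correlation of 0.5 and a paired test. The documents do not support saying that such a drift will occur, in which direction, or that the trial is bound to be positive.

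The two statements on the enrolment window conflict as written. The conflict matters here because it decides whether any calendar-time analysis is possible.

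**What to change.** 1. In Objectives, Trial design and Anticipated results, restate the aim and conclusion as estimating change in symptoms during four months of app access. State that an effect of the app is not established without a concurrent control, and drop the claim of expansion on proof of effectiveness. This costs only wording; the downside is a weaker headline claim.
2. Reconcile the enrolment window in Recruitment with the dates in Trial status.
3. Only if the longer window is real, add a sensitivity analysis that treats baseline as an outcome, for example a mixed model with calendar month and time on app, and report the month-4 change with and without the calendar term. State that it assumes similar entrants over time and does not remove retesting effects or regression to the mean. This is a different model from the planned ANCOVA, not one added term. It needs assessment dates and a rule for which month a carried-forward value belongs to, and it will lose some precision. If the window is two months, this step has no month-4 overlap to use and should be left out.
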